#### Intervention

The experimental treatment is a protocolled individual CBT program, the D(o)epressie course. It consists of 15 weekly sessions of 45 minutes, two parent sessions after 3 and 9 weeks and a meeting with the parent at the end of treatment. The D(o)epressie course is, as the CWD-A, based on the social learning theory about the aetiology of depressions by Lewinsohn [28]. According to this theory, there is a connection between the number of positive interactions between a person and his environment on one hand, and depression on the other. A triggering event such as a stressful life event causes a negative spiral of less positive interactions leading to more negative thoughts and a deteriorating depressed mood. The aim of the intervention is to reduce depressive complaints in adolescents with a depressive disorder. Since depressive episodes are multi-factorial determined, the focus of the intervention is broad. The intervention contains representative components of CBT [29] namely: psycho-education (information about depression and the rationale for the aetiology of the complaints and the treatment of them), setting attainable goals (translate large goals into realistic short term goals), self monitoring (registration of the mood, activities and thoughts), activation (planning frequent, joyful activities), improving social skills and communication skills (improvement and stimulation of social behaviour), relaxation techniques, cognitive restructuring (identifying and changing unrealistic negative thoughts about the self, others and events), role play and problem solution skills (teaching the creation of solutions for problems via brainstorm, choosing, trying and evaluating) and relapse prevention. Exercises are executed within the sessions and are generalised into daily life by means of homework assignments. In the parent sessions, parents will receive psycho education and information on CBT. Therapists are not allowed to conduct treatments in both conditions.

The control treatment consists of TAU for clinical depression. After a short telephone survey we concluded that TAU in the Netherlands consists of: Interpersonal Therapy (IPT), family therapy, parent counselling, medication, mindfulness training, acceptance commitment therapy (ACT), psychodynamic therapy (short duration), (non-directive) counselling, creative therapy and running therapy, and CBT. However, in this study CBT is not allowed within TAU. The content of TAU and the treatment techniques used, are monitored.

#### Instruments

In Table 1, concepts, source and time of assessment of all used instruments are presented. The adolescent and parent complete the self-report questionnaires online at home. Both, the adolescent and the parent have a separate login code to secure privacy. The parents fill in a paper version of the cost diary at home. The therapist completes the questionnaires at the office.

**Table 1 T1:** Instruments at different assessments and informants

	** *Domain/concept* **	** *Instrument* **	** *Items* **	** *Source* **			** *Test* **				
				** *A.* **	** *P.* **	** *T.* **	** *Pre* **	** *Med* **	** *Post* **	** *Fu1* **	** *Fu2* **
Primary outcome	Depression diagnosis	K-SADS		x	x		x		x	x	x
Secondary outcomes	Depression symptoms	CDI-II	28/17	x	x		x	x	x	x	x
	Depression severity	KSADS		x	x		x		x	x	x
		CGI-S	1			x	x	x	x		
	Depression Improvement	CGI-I	1			x	x	x	x		
	Global functioning	CGAS	1			x	x	x	x		
	Quality of life	EuroQol	6	x	x		x	x	x	x	x
	School or work	SQ	7	x			x		x	x	x
	Suicide Risk Taxation	SRT	6	x			x		x	x	x
	Comorbidity	K-SADS		x	x		x		x	x	x
		YSR	69	x			x		x	x	x
		CBCL	74		x		x		x	x	x
		SCARED	5	x	x		x		x	x	x
	Alcohol and drug use	AD	7	x			x		x	x	x
	Personality	Big 5	30	x			x		x		
	Life events	LES	23	x	x		x		x	x	x
	Parental depression	BDI-II	21		x		x		x	x	x
	Parental Psychopathology	ASR	69		x		x		x	x	x
		SCARED	4		x		x		x	x	x
	Parenting			x	x		x		x		
	-Responsivity	NOV	8								
	-Consistency	PDI	8								
	-Positive parenting	APQ	6								
	-Harsh discipline	SOG	8								
	-Psychological control	PCS	8								
	-Behavioural control	VTH	6								
	Competence	NOSI	5		x		x		x		
	Attachment	PARA	13	x	x		x		x		
	Conflict	NRI	6	x	x		x		x	x	x
Cost-effectiveness	Costs	Cost questionnaire			x		x		x	x	x
	Quality of life	EuroQol		x	x		x	x	x	x	x
Moderators	Demographic	Gender	8/12	x	x		x		x	x	x
	Characteristics adolescent	Age									
		Ethnicity									
		Education									
		Income									
	Depression severity	K-SADS		x	x		x		x	x	x
	Comorbidity	YSR			x		x		x	x	x
		CBCL		x			x		x	x	x
	Parental depression	BDI			x		x		x	x	x
	Parental Psychopathology	ASR			x		x		x	x	x
Mediators	Negative automatic thoughts	CNCEQ	16	x			x	x	x	x	x
	Cognitive Emotion regulation	CERQ	36	x			x	x	x	x	x
	Attribution style	CASQ	24	x			x	x	x	x	x
Treatment characteristics	Expectancy of treatment	PETS	7	x	x		x				
	Previous treatment	VEHI	8	x	x		x		x	x	x
	Satisfaction with treatment	SSS	4	x	x				x		
	Cooperation with treatment	CWT	5			x		x	x		
	Relationship with therapist	RWI	13	x				x	x		
	Treatment Integrity	observations							x		
	Therapy Procedures Checklist	TPC	51			x	Each session				
	Preferred treatment		1			x	x				

*Abbreviations*: *A* adolescent, *FU1* Follow-up1, *FU2* Follow-up2, *Med1* mediatortest1, *Med2* mediatortest2, *Post* posttest, *P* parents, *Pre* pretest, *T* therapist.

#### Primary outcome measures

The primary outcome measure is the presence of the depression diagnosis, as measured by the Kiddie-Schedule for Affective Disorders and Schizophrenia, present and lifetime version (K-SADS-PL) [26,27], a widely used semi-structured diagnostic interview. The K-SADS-PL assesses a wide range of diagnoses (present and life time) including their severity. The view of the adolescent, the parent and the independent clinician are taken into account. Concurrent validity of the K-SADS-PL is supported [26]. Also the interrater agreement is high (range 93% to 100%) and test –retest reliability is excellent for present and lifetime diagnoses of major depression (.77 to 100) [26]. Convergent validity of the depression screen criteria and the diagnoses generated with the K-SADS-PL was confirmed but divergent validity is only partly supported within an inpatient sample [30].

#### Secondary outcome measures

A broad range of secondary outcome measures will be assessed namely total symptoms of major depressive disorder or dysthymic disorder, severity and improvement of depression, global functioning, quality of life, suicide risk, comorbidity, alcohol and drug use, parental depression and psychopathology, parenting and conflicts. Costs, moderators, mediators and treatment characteristics will be assessed as well.

The degree of depressive symptoms are measured with a self report measure, the Child Depression Inventory-2 (CDI-2) [31,32]. The CDI-2 is a revision of the CDI [33,34] and was translated in Dutch. It was expanded with a version for the parents (CDI-P) [31] as well. The severity of the depression is rated by the independent clinician on the K-SADS-PL (see above) and by the therapist on the Clinical Global Impression-severity scale (CGI-S) [35]. Improvement of depression, in reference to the severity of the depression at the start of the treatment, is also rated by the therapist on the Clinical Global Improvement scale (CGI-I) [35]. Global functioning of the adolescent is measured by an independent clinician and therapist on the Children Global Assessment Scale (CGAS) [36,37]. The Dutch version of the EuroQol Questionaire (EQ-5D adolescent and parent version) [38] is used to establish quality of life as expressed in quality adjusted life years (QALYs). Apart from the K-SADS-PL, suicide risk is also assessed with a newly developed self-report questionnaire, which focuses on frequency of suicidal thoughts, wishes, plans and actions over the past two weeks.

Comorbidity and psychopathology is assessed with the K-SADS-PL, but also with the Youth Self Report scale (YSR) for adolescents and the Child Behavior Check List (CBCL) for parents [39,40]. Comorbidity between depression and anxiety is very high [12] therefore anxiety symptoms are also assessed separately with the Scared-5 [41].

Personality of the adolescent is assessed with the Quick Big Five Personality Inventory (QBF) [42]. For this study, we also constructed the Life Event Scale (LES) [43], which is a self-report measure about life events (including drug abuse, bereavement, maltreatment and suicide attempts), their date of occurrence and their impact on the adolescents well being.

Psychopathology of both parents is measured with the Adult Self-Report (ASR) [44]. The degree of depressive symptoms in parents is assessed with the Dutch version of the Beck Depression Inventory, second edition (BDI-II-NL) [45,46].

Parenting, in particular consistency, responsiveness, positive parenting, harsh discipline, psychological control and behavioral control is assessed with subscales of different instruments filled in by both the adolescent and the parent. The Parenting Dimensions Inventory (PDI) [47,48] was used to measure consistency, the degree to which the parent shows predictable discipline behaviour. The Nijmeegse Rearing Questionnaire (NOV) [49,50] measures responsiveness, the degree to which the parent is responsive for the needs, signals and condition of the child, and attachment, the degree to which the parent feels emotionally connected to the child. Positive parenting is measured with 6 items from the Alabama Parenting Questionnaire (APQ) [51]. The Ghent Parental Behavior Questionnaire (SOG) [52] assesses physical harsh discipline or physical punishment. Psychological control is assessed using the Psychological Control Scale (PCS) [53], which measures the degree in which the parent tries to control the child in an intrusive way. The degree in which parents monitor their children, that is behavioral control is measured with 6 items of the (Monitoring questionnaire, VTH) [54]. Competence, the parents’ perspective on their ability to address rearing practices, is established with the subscale competence of the Nijmeegse Parental Stress Index (NOSI) [55,56].

Attachment from child to parent is measured using 13 items of the Psychological Availability and Reliance on Adult (PARA) [57]. The degree of conflicts (quarrels, irritations and antagonism in the child–parent relationship) was measured with 6-item Network of relationship inventory (NRI) [58].

The economic evaluation is done by registration of costs in a cost diary based on the Trimbos Institute and Institute of Medical Technology Assessment Questionnaire on Costs Associated with Psychiatric Illness (TiC-P) [59] and PRODISQ [60]. The registered costs are directly related to health care or indirect health care (out-of-pocket costs, costs of informal care) and direct costs outside health care (monetary value of production losses caused by absence and reduced productivity). The costs will be considered separately from the perspective of mental health and from society. The mental health costs are the costs, which are credited to the mental health care budget, the decision-maker’s perspective. The societal costs are the costs of direct (mental) health care as well as indirect costs such as lost productivity, school absent and out-of-pocket costs.

Potential moderators that are analysed are severity of the depression, comorbidity, parental depression and psychopathology and demographic variables. Demographic information is gathered by adding questions about gender, age, ethnicity, education level and family income to the self-report questionnaires.

Three mediators are investigated namely negative automatic thoughts (CNCEQ) [61], cognitive emotion regulation (CERQ) [62] and attribution style (CASQ) [63]. The Cognitive Negative Cognitive Error Questionnaire (CNCEQ) measures cognitive errors namely the underestimation of the ability to cope, personalizing without mind reading, selective abstraction, over generalizing and mind reading. The Cognitive Emotion Regulation Questionnaire (CERQ) measures a broad set of cognitive emotion regulation strategies which are used in response to the experience of threatening or stressful life events; Self-blame, Other-blame, Rumination, Catastrophizing, Positive refocusing, Planning, Positive reappraisal, Putting into perspective and Acceptance. The Children’s Attributional Style Questionnaire (CASQ) is a self-report measure with three dimensions of attribution; internal- external, stable-unstable and global- specific.

Several non-specific treatment variables will be investigated. The client’s credibility, expectancy and involvement regarding treatment are assessed with the Parent Expectancies for Therapy Scale (PETS) [64] which was revised for adolescents. Previous treatments for depression, including complementary and self-help treatments, are administered with the inventory of History of Treatments (VEHI) [65]. Satisfaction with treatment is measured with the Service Satisfaction Scale (SSS) [66]. The Cooperation With Treatment scale (CWT) [67] is used to assess the degree of cooperation with treatment as observed by the therapist. The quality of the therapeutic alliance is assessed with the Therapy Alliance Scale for Adolescents (TASC) [68]. The content of treatment is assessed in both conditions with the Therapy Procedure Checklist (TPC) [69]. Treatment integrity will be established by recording two randomly chosen sessions that are observed and rated.

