#### Design

This study is designed as a multi-site, randomized controlled clinical trial in which individual CBT will be compared to TAU. Four multiple informant (adolescent, parent, therapist) assessments are done: prior to treatment (pre-test assessment), immediately after treatment (post-test assessment or after 15 sessions), 6 months after treatment (6 month follow-up) and 1 year after treatment (1 year follow-up). To investigate potential mediators two temporary assessments are conducted, each after 5 therapy sessions.

All sessions will take place within routine outpatient care within second order public mental health clinics to enhance external validity. All treatments in both conditions are delivered by psychologists with at least a master's degree-level and two years of experience within professional mental health care. These professionals are trained before delivering the treatments to enhance treatment integrity.

Adolescents who are diagnosed with a depression according to the K-SADS-PL [26,27], who meet inclusion criteria and do not meet the exclusion criteria are randomly assigned to either individual CBT or TAU. Random assignment per adolescent is executed using computer generated block randomisation and stratified per mental health centre. See Figure 2 for patient’s flow chart.

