### Statistical analyses

Missing values will be imputed. Intent-to-treat as well as completer analyses will be conducted. The effect of the intervention is analyzed with a chi-square test on the dichotomous primary outcome measure, presence of the depression diagnosis (K-SADS-PL). The cost-effectiveness analyses will be based on the comparison of costs and effects in both conditions and will be done according the international guidelines [70]. The cost- effectiveness analyses will be done separately from the perspective of mental health and society over a period of 6 months and 1 year. The effects of societal costs will be expressed in years to live, corrected for quality of life (QALYs). The costs of CBT versus CAU will be expressed in 1) incremental costs per QALY and 2) incremental costs per adolescent with a depression in full remission.

The secondary continuous outcome measures will be analyzed with repeated measures MANCOVA using the pre-test as a covariate as is recommended for RCT’s with pre-, post- and follow-up measurements [71]. For each questionnaire, the effect size (Cohen’s d) from pre- to post-treatment is defined as (M_pre_-M_post_)/SD_pooled_, where SD_pooled_ = [(SD_pre_^2^ + SD_post_^2^)/2]. CBT versus TAU pre-post effect sizes are calculated as follows [(M_CBT post_-M_TAU post_)/SD_pooled post_] – [ (M_CBT pre_-M_TAU pre_)/SD_pooled pre_]. Furthermore, analyzes will be conducted to establish clinical significance and the reliable change index [72].

Moderators will be analysed by multi-group analyses for dichotomous variables. The continuous variables will be analysed using hierarchic regression analyses. Mediator effects will be analysed using hierarchical regression analyses and structural equation modelling.

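### CGI-I is scheduled at pre-test, where its own definition gives it no meaning, and the pre-test-based analysis rules state no exception for it

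*Protocol article*

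**What the plan says.** All references are to the protocol article.

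- **Definition (Secondary outcome measures).** CGI-I is a therapist rating of change from the start of treatment: "Improvement of depression, in reference to the severity of the depression at the start of the treatment, is also rated by the therapist". The same section lists it among the secondary outcomes: "severity and improvement of depression, global functioning, quality of life".
- **Schedule (Instruments, Table 1).** The row reads "Depression Improvement CGI-I 1 x x x x". In column order this is one item, source therapist, marked at Pre, Med and Post and blank at both follow-ups.
- **Timing (Design).** The first assessment takes place "prior to treatment (pre-test assessment").
- **Analysis (Statistical analyses).** "The secondary continuous outcome measures will be analyzed with repeated measures MANCOVA using the pre-test as a covariate". The effect-size paragraph opens with "For each questionnaire, the effect size" and gives two formulas. The within-arm one divides the pre-to-post change in means by an SD pooled over pre and post. The between-arm one takes the standardised arm difference at post and subtracts the standardised arm difference at pre. CGI-I is not exempted, and no other analysis is given for it.

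**The concern.** A rating of improvement since the start of treatment cannot be made before treatment has started. A therapist faced with the item at pre-test can only enter the same neutral value for everyone or improvise. Neither is a baseline.

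The mark matters because the analysis section relies on pre-test values in three places: as covariate, in the within-arm effect size and in the between-arm effect size. If CGI-I is handled like the other repeated secondary measures, a named secondary outcome would be adjusted for a score without content and reported with effect sizes that have no clear meaning. The severity score to which CGI-I refers back is already collected: the same therapist rates CGI-S at pre-test.

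**Working it through.** **Is the pre-test mark an artefact of text extraction?** Table 1 leaves Pre blank for other measures that need treatment to have begun: satisfaction with treatment, cooperation with treatment and relationship with the therapist. Blank cells therefore survive in the text, and the authors used them for this purpose. The rows next to CGI-I (CGI-S above, CGAS below) carry the same Pre, Med and Post marks, which would fit a pattern copied down. The mark is real and conflicts with the definition.

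**Does it touch the plan's own figure?** The only computed design figure is 70 per arm. With d = 0.53, two-sided alpha 0.05 and power 0.80, the normal approximation gives 2 × (1.960 + 0.842)² / 0.53² = 55.9, so 56 per arm, and 56 / 0.80 = 70. The figure is reproduced, and CGI-I does not enter it.

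**What happens if the stated rules are applied to CGI-I?** The article gives neither scale anchors nor instructions for rating CGI-I at pre-test, so both possible cases are shown.

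*Case A: every pre-test score is the same constant c* (any c gives the same result), so `SD_pre = 0` in both arms.

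- Covariate: a model with columns for intercept, arm and pre-test has rank 2 of 3, because the pre-test column is c times the intercept. Its coefficient cannot be estimated. Dropping it leaves an unadjusted comparison of the arms.
- Between-arm effect size: the pre-test term is `(M_CBT pre − M_TAU pre)/SD_pooled pre` = (c − c)/0 = 0/0, which is undefined.
- Within-arm effect size: `(M_pre − M_post)/SD_pooled` still returns a number, but M_pre is just the constant c, and the pre-test half of the denominator is empty.

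*Case B: pre-test scores vary.* The variation cannot be change under treatment.

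- Covariate: it can be estimated but does not measure baseline severity. In a randomised trial, a pre-treatment covariate that is pure noise costs about one degree of freedom and does not bias the arm contrast.
- Between-arm effect size: it can be computed, but a standardised difference without meaning is subtracted. With 70 per arm and complete data, the sampling SE of that term is about √(2/70) = 0.17. If it is unrelated to the post score, and the post term has a similar SE, the SE of the result rises from about 0.17 to √(0.17² + 0.17²) = 0.24, with no gain in return.
- Within-arm effect size: it can be computed, but the starting mean is arbitrary.

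**The case against.** **The rules may not be meant for CGI-I.** The covariate rule speaks of continuous measures, and CGI-I is one therapist-rated item. Matching each instrument to a model is detail that an article may leave to a fuller document. This stands in part: coverage by the covariate rule is an inference, and the point is worded conditionally for that reason. The effect-size sentence reaches further, since it covers every questionnaire and the Instruments section describes therapists as completing questionnaires. The conflict between schedule and definition needs no inference.

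**The harm to the treatment comparison is minimal.** This stands. A constant covariate drops out, and a noise covariate leaves the arm contrast unbiased. CGI-I is also already expressed relative to starting severity, so it is not left without any reference to baseline. What suffers is the reported effect size and the chance to gain precision from a real baseline covariate.

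**Stronger readings that the article does not support.**

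- A reader might infer that the formulas fail outright for CGI-I. The 0/0 arises only if the pre-test SD is exactly zero in both arms, which the article does not say. The within-arm formula returns a number even then.
- A reader might infer a 41% inflation of the within-arm effect size. With `SD_pre = 0` and a square root in the pooled SD, the denominator is SD_post/√2, so d is 1.41 times the value standardised by SD_post. This needs the zero SD, a root that the formula as it stands in the text does not show, and SD_post as the yardstick. It is a conditional result and not a consequence of the plan as written.

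**Conclusion.** The point holds as a contradiction in the schedule with a limited effect on the analysis. The pre-test CGI-I score has no meaning under the article's own definition. If the general rules are applied to it, the pre-test covariate carries no baseline information and the pre-post effect sizes are not interpretable. If all pre-test scores are identical, the between-arm pre-test term is undefined.

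The size is small. One secondary outcome is affected, and depression severity is also followed by CGI-S, CDI-2 and K-SADS. The chi-square test on the primary outcome and the sample size do not change.

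Two assumptions matter. First, the general rules extend to CGI-I, which the article neither states nor excludes. Second, the absence of bias in the randomised comparison assumes that a pre-test rating used as covariate is not influenced by knowledge of the allocated arm.

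**What to change.** 1. In Table 1, remove the Pre mark from the CGI-I row.
2. In Statistical analyses, state that CGI-I is compared between arms at the mediator and post assessments, with pre-test CGI-S as covariate. The contradiction itself does not require this covariate. It is recommended because it is already collected, is the severity that the CGI-I definition refers to and can improve precision. It should be rated before the therapist knows the allocation.
3. State that the between-arm effect size for CGI-I uses the post score only, and that CGI-I is exempt from both pre-post formulas.

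The cost is one table cell and a sentence or two of text. No new data are needed, and therapists have one item fewer to complete at pre-test. If pre-test CGI-I scores have already been collected, they can simply be left out of the analysis.
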